**Flow chart of participants in the CORE trial according to CONSORT.**

Randomization will be stratified by center to balance differences in general treatment regimens between hospitals and according to the presence of an altered upper GI (esophageal, gastric or duodenal) anatomy after previous surgery. Randomization is balanced for the presence of an altered upper GI anatomy because an altered anatomy might hamper feeding tube placement and decrease success rates. Permuted-block allocation is used to provide treatment allocation in equal proportions. The block size will be subject to random variation and concealed to all investigators involved in the study.

Blinding of patients and caregivers was considered practically unfeasible given the obvious differences between the two methods of tube placement (e.g. bedside placement or placement in the endoscopy department). Moreover, the primary outcome (reinsertion of an endoscope of tube) is sufficiently objective to minimize any potential risk of measurement bias. Feeding tubes are reinserted when oral intake is less than 50% of the patient’s daily required caloric intake. This decision will be made by the treating physician, whenever possible after consulting a dietitian.

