### Statistical aspects

#### Sample size calculation

The CORE trial is designed as a non-inferiority trial, hypothesizing that the need for reinsertion of a nasoenteral feeding tube after EM guided placement is at most 10% worse as compared to endoscopic placement.

Sample size is calculated based on data from previous studies and experiences from our pilot study.

Success is defined the absence of the need for reinsertion of an endoscope or tube. We estimate a success rate of 78% in the EM guided group versus 70% in the endoscopic group. When the non-inferiority limit is set at 10%, significance level at 0.05 and power at 80%, the sample size required per study arm is 73 [18]. Taking into account a 5% loss to follow-up rate (based on previous studies), a total of 154 patients will have to be randomized in this study.

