#### Analyses

All analyses will be according to the intention-to-treat principles, meaning that all randomized patients are included in their initially assigned study arm, regardless of adherence to study protocol. The primary and secondary outcomes will be compared between the treatment groups. Results are presented as risk ratios with corresponding 95% confidence intervals. Except for the primary analysis of non-inferiority, a difference with a two-tailed P < 0.05 is considered statistically significant. In the event of imbalance between the two study arms a multivariable logistic regression will be used to correct for possible confounders. Additional as-treated and per-protocol analyses will be performed for the primary endpoint and the success rate of both tube placement methods.

A predefined subgroup analysis will be performed in patients with and without an altered upper GI anatomy after previous surgery. We will use logistic regression models to perform a formal test for interaction to assess whether outcomes differed significantly between these subgroups.

Interim analysis to evaluate serious adverse events and potentially prematurely terminate the study will not be performed, because of the perceived negligible risk associated with participation in this study.

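### Randomization is stratified by center and altered anatomy, but the only stated adjustment is an undefined, imbalance-triggered logistic model whose odds ratio is not on the scale of the 10-point margin

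*Protocol article*

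**What the plan says.** The Randomization section of the protocol article names two stratification factors. For the first: "Randomization will be stratified by center to balance differences in general treatment regimens between hospitals". For the second: "Randomization is balanced for the presence of an altered upper GI anatomy because an altered anatomy might hamper feeding tube placement and decrease success rates". Allocation is 1:1 in permuted blocks of varying size.

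The Sample size calculation section sets the hypothesis that "the need for reinsertion of a nasoenteral feeding tube after EM guided placement is at most 10% worse as compared to endoscopic placement", with these planning rates: "We estimate a success rate of 78% in the EM guided group versus 70% in the endoscopic group".

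The Analyses section says that outcomes are compared between the groups, and that "Results are presented as risk ratios with corresponding 95% confidence intervals". Its one provision for adjustment is this: "In the event of imbalance between the two study arms a multivariable logistic regression will be used to correct for possible confounders". It does not say what counts as imbalance, which variables are candidates, or which result stands if the adjusted and unadjusted ones differ. Apart from that, anatomy appears only in the subgroup interaction test. Center appears in no stated analysis.

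**The concern.** Two features of the stated rule work against the design.

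- **It depends on the data.** Whether to adjust, and for what, is settled after the arms have been compared at baseline, with no threshold and no list. In an open-label trial with a non-inferiority limit, an unadjusted and an adjusted answer are then both available.
- **It works against the stratification.** Blocked allocation within strata keeps center and anatomy close to balanced. A rule that reacts to imbalance is therefore unlikely to select the two factors that the design singled out.

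There is also a question of scale. The margin is an absolute difference, a logistic model reports an odds ratio, and the headline measure is a risk ratio. Neither ratio can be read against 10 points without a conversion, and none is described. At stake are a clear basis for the non-inferiority verdict and some precision that the stratification has already paid for.

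**Working it through.** **1. The planned sample size, and the scale of the margin.** Inputs from Sample size calculation: success 78% (EM) and 70% (endoscopic), limit 10%, significance level 0.05, power 80%, loss 5%. The side of the test is not stated.

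n per arm = (z_alpha + z_power)² × [p1(1−p1) + p2(1−p2)] / (margin + p1 − p2)²

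- Absolute margin 0.10, one-sided 0.05: (1.645 + 0.842)² × (0.1716 + 0.2100) / 0.18² = 72.8, so 73. Total 146/0.95 = 153.7, so 154. Both stated figures are reproduced.
- Absolute margin, one-sided 0.025: 93 per arm, 196 in total.
- Relative 10% margin, one-sided 0.05: 105 per arm (7 points on 70% success) or 195 per arm (3 points on 30% reinsertion).

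Of these variants, only an absolute 10-point margin at one-sided 0.05 matches the plan.

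**2. The margin on the ratio scales.** With control reinsertion p and margin p + 0.10, RR = (p + 0.10)/p and OR = [(p + 0.10)/(0.90 − p)] / [p/(1 − p)].

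| Control reinsertion | RR at the margin | OR at the margin |
|---|---|---|
| 20% | 1.50 | 1.71 |
| 30% (planned) | 1.33 | 1.56 |
| 40% | 1.25 | 1.50 |

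Fixing the planned equivalents does not hold the margin at 10 points. OR 1.556 allows 8.0 points at a 20% control rate and 10.9 at 40%. RR 1.333 allows 6.7 and 13.3. An adjusted odds ratio also differs from the marginal one even under perfect balance. For assumed anatomy gaps of 0.2 to 0.4 and 30% or 50% altered anatomy, a marginal OR of 1.556 corresponds to a conditional OR of about 1.59 to 1.75.

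**3. What ignoring the strata costs.** Stratified allocation already removes between-stratum variation from the observed difference. An unadjusted standard error does not credit this and is too large. This was simulated with 73 per arm, 200,000 runs, an altered-anatomy share of 20% to 50% and a gap in success between anatomy strata of 0.2 to 0.4. Share and gap are assumptions, because the article gives neither. Center was not simulated.

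| | Unadjusted | Stratified by anatomy |
|---|---|---|
| Type I error at the margin (nominal 0.05) | 0.0335 to 0.0456 | 0.0515 to 0.0537 |
| Power at 78% v 70% | 0.803 to 0.830 | 0.816 to 0.881 |

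With no gap, the type I error is 0.048–0.049 unadjusted and 0.050–0.051 stratified, and the power is 0.80 and about 0.81.

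**4. The same cost as a share of variance.** Let f be the share with altered anatomy, pa and pn the reinsertion risks with and without it, and p = f·pa + (1−f)·pn. The share removed is R = f(1−f)(pa−pn)² / [p(1−p)], and the patient-equivalent is 154 × R/(1−R). All inputs are assumed.

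- f = 0.3, 0.30 v 0.20: 0.21 × 0.0100 / 0.1771 = 1.2%, about 2 patients.
- f = 0.3, 0.40 v 0.20: 0.21 × 0.0400 / 0.1924 = 4.4%, about 7 patients.
- f = 0.4, 0.42 v 0.10: 0.24 × 0.1024 / 0.1760 = 14.0%, about 25 patients.
- f = 0.4, 0.45 v 0.10: 0.24 × 0.1225 / 0.1824 = 16.1%, about 30 patients.

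**The case against.** The strongest reply is that the article names no test for the primary non-inferiority analysis, and that a fuller protocol or SAP may include the strata. That stands as far as the silence goes: one cannot say that the primary analysis is definitely unadjusted. It does not cover the imbalance sentence, which is a stated rule and a poor one. It is also fair that baseline imbalance can be judged without outcomes, and that the article does not say the adjusted result would replace the primary verdict. Equally, it does not say that it would not.

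A reader might infer more than the document supports:

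- **That the trial would have too many false positives or miss its planned power.** The simulation shows the opposite. The unadjusted test is conservative and its power is at or above 80%. The stratified test sits slightly above nominal.
- **That a logistic model can never be set against the margin.** It can, if standardized to a risk difference. What is missing is the conversion, and the planned risk ratio has the same gap.
- **That the article declares anatomy prognostic.** It says only that it might lower success. The nearest figure, in Background, is 58% EM placement success with altered anatomy. That comes from a retrospective cohort, for one technique and a different outcome.
- **That the imbalance model would be badly overfitted.** At the planned rates there are about 154 × (0.22 + 0.30)/2 = 40 reinsertions, against 11 variables in Descriptive statistics. But nothing says that all of them would enter the model.

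**Conclusion.** The point holds as an avoidable weakness in the stated analysis, not as a threat to validity. The imbalance rule is undefined and data-dependent, is unlikely to pick up the design factors, and reports on a scale that does not match the margin. The scale finding rests on the document's own figures, because 73 per arm and 154 in total imply an absolute margin. The precision forgone is uncertain: about 1% to 16% of the variance, or roughly 2 to 30 patient-equivalents out of 154. It depends wholly on an assumed share of altered anatomy (30% to 40%) and an assumed gap between anatomy strata (10 to 35 points). If anatomy and center turn out not to be prognostic, the gain is close to nil. The change is worth making because it settles in advance which number decides non-inferiority.

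**What to change.** - Prespecify the primary non-inferiority analysis as a risk difference stratified by altered anatomy and center, either Mantel-Haenszel or a logistic model standardized to the risk difference. State in advance the rule for pooling small centers.
- Compare its confidence limit with 10 points, using an interval whose level matches the one-sided alpha. The sample size implies one-sided 0.05, which is a two-sided 90% interval. If the team prefers the limit of a 95% interval, 73 per arm gives about 70% power at the planned rates, and that should be stated.
- Delete the imbalance trigger.
- Make any further covariate adjustment a sensitivity analysis, with covariates named in advance, on the risk-difference scale, and state that it does not decide non-inferiority. Risk ratios can stay as a supplementary summary.

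The cost is a short change of wording and slightly more analysis work. The stratification data already exist and the sample size does not change.

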### Dissemination policy

The trial’s results will be submitted to a peer-reviewed journal regardless of the outcome. Co-authorship will be based on the international guidelines with a maximum of three co-authorships per participating center. Participating clinicians that do not fulfill these criteria will be listed as ‘collaborator’ and the journal will be asked to present the names of all collaborators to be listed in PubMed. The order of authors will be based primarily on scientific input and secondarily on the number of randomized patients.

## Discussion

The CORE trial is initiated by gastrointestinal surgeons and gastroenterologists based on the potential benefits of EM guided tube placement (e.g. reduced patient discomfort and costs). The study is designed as a multicenter, randomized controlled non-inferiority trial to answer the question whether EM guided nasoenteral feeding tube placement is at least as effective as endoscopic placement in surgical patients. Superiority would, of course, be preferred, but such a trial would be practically impossible given the required sample size of nearly a thousand patients. Moreover, superiority regarding effectiveness is not required, since EM guided nasoenteral tube placement may still be recommended if its effectiveness is similar, or at least not worse than the non-inferiority limit, to endoscopic tube placement, because of the intrinsic advantages of this technique [19].

In contrast to previous studies on EM guided nasoenteral feeding tube placement, the CORE trial is an investigator-initiated randomized controlled multicenter trial comparing EM guided placement to the current conventional tube placement method (endoscopy). Moreover, it does not only focus on successful tube placement, but also on patient-reported outcomes and costs. When looking at effectiveness, the success rate of initial tube placement would have been the most obvious primary outcome. However, since passage of the tube through the naso- and oropharynx is considered to be the most burdensome part of tube placement, a reduction in reinsertions of the tube seems much more relevant to the patient. In addition, the success of tube placement is included in this outcome because reinsertion is required after failure. Furthermore, EM guided tube placement might lead to a slight reduction in necessary reinsertions, since tubes dislodged into the stomach can be repositioned without removal of the tube (as is the case with endoscopic replacement).

The study population consists of patients admitted to gastrointestinal surgical wards who are in need of nasoenteral feeding whereas previous randomized controlled trials (and the majority of cohort studies) have only been performed in critically ill patients. This population is chosen because the incidence of gastroparesis is relatively high in these patients, since their GI system is frequently disordered by an operation, postoperative complications or the underlying or concomitant disease. Gastroparesis is especially a problem in patients after abdominal surgery and many feeding strategies have been investigated [20-22]. The high incidence of gastroparesis may not only lead to a frequent need for nasoenteral feeding, but it also hampers post-pyloric tube placement due to gastric stasis. Moreover, in a substantial subset of surgical patients the upper GI anatomy is altered due to surgery, which may complicate tube placement as, consequently, also the route of the feeding tube has changed. When a nasoenteral feeding tube placement method would prove to be successful in the surgical population, the results can probably be extrapolated easily to the overall hospital population requiring nasoenteral feeding.

In conclusion, the CORE trial is a randomized controlled multicenter trial, which will generate evidence on the effectiveness of EM guided placement of nasoenteral feeding tubes in surgical patients and its related costs as compared to endoscopic placement, and can potentially offer a strong argument to further implement this technique as method of choice for placement of nasoenteral feeding tubes.

## Trial status

The first patient was randomized on the 13th of March 2014. As of February 23rd 2015, 133 of 154 patients (86%) have been randomized and inclusion is progressing according to schedule.

## Abbreviations

ASA: American society of anesthesiologists
CORE: Electromagnetic guided or endoscopic nasoenteral feeding tube placement in surgical patients
CRF: Case report form
EM: Electromagnetic
GI: Gastrointestinal
VAS: Visual analogue scale
